## Abstract

**Background:**

Maternal smoking and stress during pregnancy are associated with adverse health effects for women themselves and are risk factors for adverse developmental outcomes of the unborn child. Smoking and stress seem to be intertwined in various ways. First, the majority of smoking pregnant women is of lower socio-economic status, which is associated with higher levels of perceived stress. Second, smoking women often report to smoke because they feel stressed. Third, quitting smoking often increases perceived stress levels initially. Therefore, effective interventions are needed to support women with smoking cessation by reducing stress. The aim of this study is to test the effectiveness of an eHealth intervention on stress reduction and smoking cessation.

**Methods/design:**

The Stress- and Smoke Free Start of Life (SSFSL) study is a randomized controlled trial (RCT) comparing a personalized eHealth intervention with a control condition. Inclusion criteria for the women are: (1) > 18 years of age, (2) < 28 weeks pregnant at recruitment, (3) currently smoking. Consenting participants will be randomly assigned to the intervention or control group. Participants allocated to the intervention group will receive an 8-week intervention delivered on their smartphone. The application includes psycho-education on pregnancy, stress, and smoking (cessation); stress-management training consisting of Heart Rate Variability-biofeedback; and a personalized stop-smoking-plan. Participants in the control condition will be invited to visit a webpage with information on pregnancy, stress, and smoking (cessation). Study outcomes will be collected via online questionnaires, at four timepoints: pre-intervention (baseline; t0), post-intervention (8 weeks + 1 day after t0; t1), follow up at two weeks after birth (t2), and follow up at three months after birth (t3). The primary outcome measure is self-reported smoking cessation. Secondary outcomes include daily self-reported number of cigarettes smoked, perceived stress, pregnancy experience, birth outcomes, and negative affectivity scores of the baby. Moreover, the mediating effect of stress reduction on smoking cessation will be examined, and possible moderators will be tested.

**Discussion:**

If the eHealth intervention is effective in smoking cessation among pregnant smoking women, it can be implemented as a tool into the health care in the Netherlands.

**Trial registration:**

Netherlands Trial Register, ID: NL8156. Registered on 11 November 2019.

## Introduction

Worldwide, substantial numbers of women who smoke, continue to smoke during pregnancy. Recently estimated prevalence of smoking pregnant women in the European Region was 8.1%, which was the highest percentage when compared to the world average of 1.7% [1]. Even though prevalence rates of pregnant smoking women have been decreasing over the years [2], these numbers are yet of concern for several reasons. Maternal smoking has serious implications for the developing fetus and the mother. Maternal smoking increases the risk of miscarriage [3], premature delivery, lower birth weight [4], and congenital abnormalities [5]. Among the single newborns born in the Netherlands with small-for-gestational age, 17% of the cases was found to be related to maternal smoking during pregnancy [6]. Negative effects of prenatal maternal smoking are not only observed in the early years of the child, but have also been associated with negative health outcomes later in life, such as asthma [7] and obesity [8]. Moreover, maternal smoking during pregnancy has been linked to reduced academic achievement and decreased cognitive abilities of children [9, 10] and to neurobehavioral problems in childhood [11–13].

Despite the growing body of evidence on the negative consequences of prenatal smoking for child development and despite extensive efforts to reduce the prevalence of prenatal smoking, a relatively large group of expecting mothers continues to smoke during pregnancy [1]. Factors associated with continued smoking during pregnancy are socioeconomic status (SES), nicotine dependence, and stress experienced during pregnancy [14, 15]. In general, women of low SES experience socioeconomic inequalities when it comes to financial resources, stability in living situation, general health, including more stress-related health problems and unhealthy lifestyle habits such as smoking [16, 17]. Stress plays an important role in initiating smoking and maintenance of smoking [18, 19]. According to the stress-coping model, smoking causes a temporarily reduction of negative affect and an increase in positive affect, which can be an explanation for the use of smoking as a coping strategy in situations of high stress [20]. Neurobiological models of addiction suggest that both stress and nicotine exposure trigger stress and reward circuits in the brain explaining why stress can increase the urge to smoke [18]. Moreover, high levels of stress hinder changing unhealthy lifestyle behaviors, such as smoking [21]. Increased activation of brain stress systems are thought to reduce an individual’s ability to cope with extra stressors and may strengthen the effects of acute nicotine exposure during abstinence, thereby contributing to the increased vulnerability to relapse caused by stress during periods of abstinence [19]. Elevated stress levels may thus explain why expecting women may fail to quit smoking, because pregnancy is a critical life event. Indeed, during pregnancy, many women experience some additional levels of psychosocial and pregnancy-related stress [22], due to physical changes related to pregnancy, concerns about childbirth and parenting, or relationship difficulties. These extra pregnancy related stressors can thus make smoking cessation even more challenging.

While stress thus seems to be a maintaining factor of smoking, stress experienced during pregnancy itself has also been associated with adverse offspring outcomes. Research has shown that prenatal stress is associated with delayed motor and mental development, and temperamental variation in infants and older children [23–26]. In addition, pregnancy-specific anxiety predicted more difficult child temperament, as indicated by negative emotional reactivity, fearfulness and falling reactivity [27].

Thus, as prenatal stress and smoking are both related to negative child outcomes, and stress seems to play a role in the maintenance of smoking, interventions targeting both stress and smoking may be highly effective. Unfortunately, existing programs aimed at smoking cessation have been mostly ineffective with high relapse rates, specifically among vulnerable women with low SES and high levels of perceived stress [14, 28, 29]. An important element that is missing in most smoking cessation programs thus far, is stress management. This element seems essential for smoking cessation programs, especially those targeting low SES women, since effective stress-coping techniques may help women quit smoking during pregnancy and reduce long-term relapse risk. Investing in relapse prevention is important, because relapse within the first six months after birth is common, with a pooled mean proportion of women that have re-started smoking at 6 months of 43% [30].

A method that has shown to reduce stress is Heart Rate Variability-biofeedback (HRV-BF) [31]. HRV is determined by the variation in time between consecutive heartbeats as assessed by the interval between successive R-wave peaks in an electrocardiogram (ECG). Higher HRV has been associated with more favorable physical and mental health outcomes [32–34]. The aim of HRV-BF is to increase HRV and stimulate cardiac regulation [35]. HRV is influenced by physiological factors such as respiration, and respiratory sinus arrhythmia (RSA) is the component of HRV that reflects the variation in heart rate due to respiratory activity [35]. A mechanism that regulates cardiac activity is the baroreflex [36], which activity is triggered by changes in blood pressure in the body’s large blood vessels in order to achieve homeostasis [35]. Physiological activity, such as breathing, affect baroreflex functioning [34]. Through HRV-BF, people learn a method of paced breathing with visual feedback about their HRV in order to detect the frequency at which HRV is maximized. Maximized HRV causes increases in baroreflex amplitude, which can improve reflex efficiency and, in turn, can positively affect autonomic activity modulation [36].

Recent research of our team showed that HRV-BF training was effective in reducing feelings of stress in pregnant and non-pregnant women [37]. These results are in line with a meta-analysis, including community and clinical adult samples, reporting that HRV-BF was associated with a large reduction of self-reported stress and anxiety [38]. HRV-BF may be regarded as an effective stress-reduction intervention, and may be beneficial for pregnant women to support them quit smoking while suffering from stress.

During the last decades, more and more health care is being offered via the Internet, for instance by means of eHealth platforms [39, 40]. Benefits of eHealth are the high accessibility for a large group of people and the usually low cost it entails. Moreover, eHealth is unrestricted by time and place and might reach populations that otherwise do not ask for support, for instance as a result of possible stigmatization. As stigmatization is a common problem among pregnant smoking women [41], and considering the many benefits of eHealth for this group [42], an app-intervention to support pregnant women quit smoking is promising. A recent systematic review supports this, as results show that eHealth approaches were moderately effective on smoking abstinence in a general population of adult smokers [43]. They also emphasize the use of an interactive and tailored approach of smoking cessation interventions.

Considering the benefits of eHealth, we have developed an application including HRV-BF, targeting pregnant women who want to quit smoking. HRV-BF is easy to learn and maintain in daily life, and at the same time requires little efforts. Thus, HRV-BF could be highly appropriate for pregnant smoking women with low SES, who would like to quit smoking. In order to gain knowledge about the underlying mechanisms and conditional factors of treatment effectiveness, various factors that are associated with stress and smoking need to be studied. Factors that may affect the treatment effect obtained in stress reduction and smoking cessation are: pregnancy experience [21], pregnancy-related anxiety [44], self-efficacy regarding smoking cessation [45], a person’s motivation to quit smoking [46], and COVID-19 related stress [47]. Moreover, focusing on indirect treatment effects is also relevant in this transitional and developmental context. For example, factors associated with parenting, such as parenting self-efficacy [48–50] and the bond that the mother feels with her child [51, 52] may also increase when women experience less stress and quit smoking. Parenting factors such as parenting self-efficacy and a warm mother-child bond have been associated with positive effects on child development (e.g. [48, 53]).

### The current study

The current study will examine the effectiveness of a personalized 8-week lasting eHealth intervention “Together with Eva”, consisting of adapted parts of existing quit-smoking and stress-management interventions and an HRV-BF prototype application by means of a randomized controlled trial. “Together with Eva” includes psycho-education on stress, smoking (cessation), and pregnancy; a personalized stop-smoking plan; stress reducing exercises, comprising of HRV-biofeedback, and problem-solving techniques. Participants in the control group will receive access to a webpage developed for this study where they can read information comparable to the psycho-education of the intervention group. This information is however summarized and not interactive. Overall, the main research question of this study is the following:
Is the app intervention “Together with Eva” an effective intervention to support pregnant women to quit smoking during pregnancy and stay abstinent after giving birth? The primary outcome measure is self-reported smoking cessation. Secondary objectives of this study are to investigate whether;the intervention is effective on secondary outcomes (i.e. smoking behavior, perceived stress, birth outcomes, negative affectivity, parenting self-efficacy, pregnancy-related anxiety, feelings of mother-child bonding, and COVID-19 related stress),the intervention effect on smoking cessation is mediated by the reduction of perceived stress, and whether;variables such as program usage and experience, self-efficacy regarding smoking cessation, intrinsic motivation for life style behavior change, and pregnancy experience moderate the treatment effect.

## Methods and analysis

### Trial design

This study is a two-arm, parallel, single blinded randomized controlled trial (RCT) including four measurement waves: pre-intervention or baseline (t0), post-intervention (t1), two weeks following birth (t2) and three months after birth (t3). Pregnant, smoking women will be randomized to one of two groups: 1) personalized eHealth intervention (“Together with Eva”) on the smartphone followed for 8 weeks; or 2) active control condition which includes psycho-education on stress, smoking, and pregnancy through a website. The protocol is developed in accordance with the Standard Protocol Items: Recommendations for Interventional Trials guidelines (SPIRIT; Fig. 1). The trial is registered with the Netherlands Trial Register on November 112,019. The registration ID is NL8156. Ethical approval was obtained from the Medical Ethical Committee of the VU Medical Center (METc VUmc 2020/065/NL71342.029.20).

**Fig. 1 Fig1:**
[figure not shown]
SPIRIT Flow Diagram of the Stress And Smoke Free Pregnancy Study

### Participants and recruitment procedure

Participants will be recruited through midwifery practices, specialized departments of hospitals in the Netherlands and through advertisements on reliable websites focusing on pregnancy over a 1.5-year period (July 2020–February 2022). Health care professionals will be offered flyers to hand out to potential participants. Additionally, they will receive an information sheet with the inclusion criteria, short sentences for study explanation, and a list of frequently asked questions so that they can easily explain the study to potential participants. Women are eligible for participation if they are older than 18 years, are less then 28 weeks pregnant (to enable intervention completion in view of the risk for premature birth in pregnant smokers), if they smoke on a regular basis (at least smoking 1 day/week), have an intention to quit smoking during pregnancy, and if they have sufficient command of the Dutch language. Women with severe psychiatric disorders, women who abuse other drugs (e.g. alcohol, cannabis, cocaine, and GHB), and who are participating in other intensive stop-smoking interventions will be excluded from participation. The focus of our recruitment will be on women with low SES. However, women with high SES are also allowed to participate.

### Sample size calculation

To ensure acceptable power for the main analysis of the intervention effect on smoking cessation at post-intervention, an a priori sample size calculation was performed by the program G*Power [54]. Using a power of 80% an alpha of 0.05 and an F-test, we need to include 160 participants (80 participants in each arm) in order to be able to detect a small difference (effect size of 0.20) between the intervention group and the control group on the primary outcome measure, smoking cessation at t1.

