### Procedure

The participants will be informed about the study via obstetric practices, gynecologists, or general practitioners, but can also sign up for participation by own registration via a form on the project’s website. Pregnant women, who are visiting their health professional, will be given a brief explanation via a flyer. Women, who are willing to participate, will be asked to scan the QR-code on the flyer and will then be directed to an online registration form where they will fill in the contact details. This information will then be sent to a secured mailbox which can only be accessed by the main researcher. Subsequently, registered participants will be called by the researcher or research assistant who will explain the study in more detail. If participants are willing to participate they will be sent an information letter and consent form, which they will be asked to read, sign and send back. Then, women will be called to screen for exclusion criteria. Eligible women will receive an invitation email with a link to the first online questionnaire (t0). Participants will be assigned an identification number, which will be used throughout the study. To ensure confidentiality, the file including both the participants’ names and identification numbers will be saved with a password that can only be accessed by the principal researcher. After completion of the t0 questionnaire, participants will be randomized. This will be done by sending an email to an independent researcher who has access to the randomization list. The randomization list is created with blocks of 2, 4, and 6 participants, each containing equal numbers of participants allocated to the intervention and active control group, using an online randomization program. The independent researcher will send an email with information about the assigned group. Participants assigned to the intervention group receive an email with a link to download the application on their smartphones. The control group will be sent a link to the website with the psycho-education module, which they can access as frequently as they desire. After 8 weeks, participants will receive an invitation to complete the second questionnaire (t1). Two follow-up questionnaires will be sent, the first at two weeks after birth (t2) and the other at three months after birth (t3). Participants will receive 7.50 euros on their bank account for each completed questionnaire.

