### Outcome measures

At four different time points, women will receive online questionnaires. Each questionnaire will take approximately 15–20 min to complete. The first questionnaire is a baseline questionnaire (t0, before randomization) including the main outcomes and demographic information (i.e. date of birth, weeks of pregnancy, ethnicity, educational level, employment status, relationship status, smoking behavior partner, living conditions). Eight weeks and one day after group assignment, participants will receive the second questionnaire (t1), through which post-intervention measurements will take place. Follow-up questionnaires will be sent two weeks after birth (t2) and three months after birth (t3). In Fig. 1, an overview of the outcome measurements for each time point is depicted. Prior to t1, t2, and t3, a screening question will appear asking about the health of the baby. In case of pregnancy loss or if the baby died after birth, participants will be advised to quit the study participation. They will still receive the agreed compensation for the completed questionnaires.

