### Statistical analyses

The study will be performed according to the Consolidated Standards of Reporting Trials (CONSORT) Statement (see Fig. 3). All analysis will be done in SPSS version 26.0 and ﻿RStudio version 1.1.456 and a significance level of 0.05 will be used. Analyses will be performed conforming to intention-to-treat analysis, so that all randomized participants will be analyzed. We will explore baseline data to examine differences between the two different conditions and between the study completers and drop-outs. We will control for relevant covariates (i.e. SES, treatment history, maternal age, gestational age at birth, level of addiction, birth complications, way of delivery) by adding them to the models. Prior to the main analyses, outliers will be checked. Demographic outcomes will be compared using chi-square tests and independent sample t-tests.

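### The 160 women required by the t1 power calculation are also the 160 to be included, so the stated 80% power leaves no room for loss before t1

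*Protocol article*

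**What the plan says.** The Sample size calculation section of the protocol article describes a G*Power calculation: "Using a power of 80% an alpha of 0.05 and an F-test". The target is a "small difference (effect size of 0.20") between the arms on the "primary outcome measure, smoking cessation at t1". Its result is given as the enrolment figure: "we need to include 160 participants (80 participants in each arm"). The section names no attrition rate, no inflation and no separate number of women expected to have an outcome.

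Three other places bear on whether 160 enrolled women will give 160 answers at t1:

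- Procedure: "After completion of the t0 questionnaire, participants will be randomized". Loss between t0 and t1 therefore falls after randomisation and comes out of the 80 per arm.
- Statistical analyses: "We will explore baseline data to examine differences between the two different conditions and between the study completers and drop-outs". The same section promises an intention-to-treat analysis of everyone randomised.
- Outcome measures: the t1 answer comes from an online questionnaire sent eight weeks and one day after group assignment. It is preceded by a screening question on the baby's health. "In case of pregnancy loss or if the baby died after birth, participants will be advised to quit the study participation".

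**The concern.** A power program returns the number of observations that enter the test. If that number is also the number enrolled, the quoted power applies only when every enrolled woman supplies the outcome. Here the outcome is one self-report item in an online questionnaire about two months after randomisation, and the article makes provision for women who will not complete it.

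What is at stake is how the result is read. A non-significant difference would be presented as coming from a trial with 80% power for its chosen effect, when the power for that effect was lower by an amount that depends on the response at t1.

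**Working it through.** **Inputs from the article.** Power 80%; alpha 0.05, in the sample size section and again under Statistical analyses ("a significance level of 0.05 will be used"); an F-test; effect size 0.20 with the metric not named; 160 women, 80 per arm; endpoint cessation at t1.

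**Input not in the article.** The share of women without a t1 answer. I assume 5%, 10%, 20% and 30%, equal in both arms.

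**Step 1: the article's own figure.** For a two-group F-test with degrees of freedom 1 and N − 2, the noncentrality is λ = N·f². With f = 0.20 and N = 160, λ = 160 × 0.04 = 6.4 and power is 71.0%. Reaching 80% takes 199 women, or 200 with equal arms. So 160 does not reproduce from f = 0.20 with a one-way F-test. That is a separate point. To keep it out of this one, I grant the article its 80% at 160 and solve for the effect that delivers it: f = 0.2228, λ = 160 × 0.2228² ≈ 7.95.

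**Step 2: lose women before t1.** Keep f = 0.2228, set N = 160 × (1 − loss), and recompute the power.

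| Loss by t1 | Women with a t1 answer | λ = N·f² | Power |
|---|---|---|---|
| 0% | 160 | 7.95 | 80.0% |
| 5% | 152 | 7.55 | 77.9% |
| 10% | 144 | 7.15 | 75.7% |
| 20% | 128 | 6.36 | 70.6% |
| 30% | 112 | 5.56 | 64.7% |

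**Step 3: does this depend on the F-test?** Hardly. For any test whose statistic is roughly normal and which has 80% power at 160, the standardised effect is 1.96 + 0.84 = 2.80, and it shrinks with the square root of the sample. At 20% loss, 2.80 × √0.8 = 2.51, and Φ(2.51 − 1.96) = Φ(0.55) ≈ 71%. A two-proportion z-test set to 80% at 80 per arm gives 77.9%, 75.7%, 70.6% and 64.7% (rounded to one decimal from 0.779, 0.757, 0.706 and 0.647) at the four loss rates.

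**Step 4: count non-responders as smokers.** This keeps 80 per arm in the analysis but multiplies both quit rates by (1 − loss). The article gives no quit rates, so I assume 15% in the control arm and solve for the intervention rate that gives 80% power at 80 per arm: 33.9%.

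| Loss by t1 | Observed quit rates | Power |
|---|---|---|
| 5% | 14.3% vs 32.2% | 77.2% |
| 10% | 13.5% vs 30.5% | 74.2% |
| 20% | 12.0% vs 27.1% | 67.7% |
| 30% | 10.5% vs 23.7% | 60.5% |

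In this example the power is lower at every loss rate than when non-responders are dropped.

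**The case against.** **An allowance may exist in a document not shown.** The article condenses a fuller protocol, and its flow diagram is not available here. The request is therefore not for an omitted detail. The article puts a definite power against a definite enrolment and presents the second as what the first requires. Nothing in its text suggests that 160 already includes an allowance.

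**A reader might infer that power falls below 80% whatever effect size or test lies behind the calculation.** The documents do not support that. It holds only if 160 is the number needed for exactly 80%. A larger assumed effect can absorb loss: quit rates of 10% and 30% still give 81.5% with 64 per arm, which is 160 less 20%. Such inputs conflict with the statement that 160 are needed, but they rule out a universal claim.

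**A reader might also infer that the plan expects heavy loss by t1.** It does not say so. The comparison of completers and drop-outs covers a study that runs to three months after birth, and the advised exit includes deaths after birth, so part of this loss falls after t1. Participants are paid per questionnaire, which favours retention. At 5% loss the shortfall is about two points. The intervention arm also receives weekly calls and reminders, so equal loss in both arms is a simplification.

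**Intention-to-treat and the planned GEE soften the loss.** Analysing everyone randomised does not supply a missing t1 answer, and Step 4 shows that counting it as smoking lowers the power. A woman who misses t1 but answers t2 or t3 can still contribute to the GEE, and that part of the objection stands. The stated power, however, is for cessation at t1, and a later answer does not replace that one.

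**Conclusion.** The point holds in conditional form. If 160 women with data give 80% power at t1, as the article says, then enrolling 160 gives less than 80% once t1 response is incomplete, and the article itself provides for incomplete response. Its size cannot be fixed from the documents. Illustratively, the shortfall runs from about 2 points at 5% loss to about 15 points at 30%, assuming equal loss in both arms and an effect that 160 complete women would detect with 80% power.

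These figures are not this trial's actual power. On the plain reading of the printed inputs (f = 0.20, one-way F-test) the power is 71.0% before any loss, and 66.4%, 61.2% and 55.5% at 10%, 20% and 30%. That discrepancy needs its own correction. Correcting it alone would still leave the number required equal to the number enrolled.

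**What to change.** In the Sample size calculation section:

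1. State that 160 is the number randomised.
2. State the share expected to give a t1 smoking answer, with its basis.
3. Replace the unqualified 80% with the power for that share, shown at 5%, 10%, 20% and 30% loss and computed from the effect size and test actually used.
4. If 160 already contains an allowance, give the number of women with data on which it was based.

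Possible wording, if the 80% at 160 is confirmed: with 20% loss by t1, 128 of the 160 randomised women have an outcome, and power is about 71% for the effect that 160 complete women would detect with 80%.

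The cost is a few sentences and a less favourable stated power. No additional enrolment is requested, and neither the conduct of the trial nor the analysis changes.

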#### Primary outcome

##### Smoking cessation

Smoking cessation and abstinence will be assessed using a self-report question ‘Do you smoke?’ (yes/no). If answered with ‘yes’, an additional question asking whether she smokes on a daily basis will indicate the frequency of the smoking behaviour.

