**Fig. 3 Fig3:**
[figure not shown]
Consolidated Standards of Reporting Trials (CONSORT) flow diagram

To examine the effectiveness of the eHealth intervention on the primary outcome, the number of women who quit smoking during pregnancy measured at post-intervention and follow-up, General Estimating Equations (GEE) using a logistic model will be performed. Potential covariates that will be included in the model are maternal age, depressive symptoms, gestational age, employment status, education level, level of addiction, and partner’s smoking status. To investigate the effectiveness of the intervention on secondary outcomes (i.e., smoking behavior, perceived stress, birth outcomes, negative affectivity, self-efficacy, mother-child bonding, intrinsic motivation, parenting self-efficacy, pregnancy-related anxiety) linear mixed models will be performed for each outcome variable separately. Furthermore, we will test whether the effect of the intervention (independent variable) on smoking cessation (dependent variable) is mediated by a change in perceived stress using a GEE model. Moreover, it will be tested whether program usage and experience, self-efficacy regarding smoking cessation, feelings of mother-child bonding, intrinsic motivation for life style behavior change, and pregnancy experience moderate the effect on smoking cessation (primary outcome), smoking behaviour, and perceived stress by adding the variables to the GEE model.

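### The sample size of 160 does not follow from the stated inputs (F-test, effect size 0.20, 80% power at t1), and an F-test does not match the yes/no outcome analysed by logistic GEE

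*Protocol article*

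**What the plan says.** The Sample size calculation section reports an a priori G*Power calculation for the main analysis of smoking cessation after the intervention. Its settings are: "Using a power of 80% an alpha of 0.05 and an F-test". Its result is the need to "include 160 participants (80 participants in each arm) in order to be able to detect a small difference (effect size of 0.20" on the primary outcome, and the section names t1 as the time point. It does not name the effect-size metric, the G*Power procedure, a number of repeated measures, a correlation, a covariate R-squared or a quit rate for either arm.

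The Primary outcome section makes the endpoint binary: "Smoking cessation and abstinence will be assessed using a self-report question" with a yes/no answer. The Statistical analyses section says that for this outcome, measured after the intervention and at follow-up, "General Estimating Equations (GEE) using a logistic model will be performed". Covariates are to be added. The same section confirms that "a significance level of 0.05 will be used".

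**The concern.** The article gives the test, alpha, power, effect size, time point and sample size together, so they can be checked against each other. They do not agree. The effect size also belongs to a comparison of means, while the endpoint is a proportion. A reader therefore cannot tell what difference in quit rates the trial was built to detect.

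At stake is how the result will be read. If the article's claim is taken at face value, a non-significant result at t1 could be read as evidence against a small benefit, when the stated design may have well under 80% power for one.

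**Working it through.** **Inputs.** From Sample size calculation: two arms of 80, alpha 0.05, power 80%, F-test, effect size 0.20, one time point (t1). With two groups the F-test has 1 numerator degree of freedom and is non-directional.

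**Attempt to reproduce 160.** For a two-group F-test the noncentrality is λ = f² × N, with 1 and N − 2 degrees of freedom. At these sample sizes, 80% power needs λ of about 7.9 to 8.0.

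| Reading of 0.20 | λ at N = 160 | Power at 160 | N for 80% power |
|---|---|---|---|
| Cohen's f (the metric of G*Power's ANOVA F-tests) | 0.04 × 160 = 6.4 | 71.0% | 199, or 200 balanced |
| Cohen's d, so f = d/2 = 0.10 | 0.01 × 160 = 1.6 | 24.2% | 788 |
| Chi-square, w = 0.20 | 0.04 × 160 = 6.4 | 71.6% | 197 |
| Cohen's h = 0.20 (two proportions) | – | about 24% | 786 |

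None gives 160. Under the f reading, the smallest effect detectable with 160 is about f = 0.223. Spending degrees of freedom on one to four covariates, without any gain in explained variance, still needs 199.

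**Settings that do give 160.** Each of the F-test routes below raises λ from 6.4 to 8.0 by an assumption that is not in the text.

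- Repeated-measures between-group F-test, λ = f² × N × m / (1 + (m − 1)r):
  - m = 2, r = 0.6: 6.4 × 2 / 1.6 = 8.0.
  - m = 3, r = 0.7: 6.4 × 3 / 2.4 = 8.0.
  - m = 4, r of about 0.73 also gives 160.
  - With r = 0.5 the required N would be 150, 134 or 126 for 2, 3 or 4 waves.
- ANCOVA with covariates explaining 20% of the variance: 6.4 / (1 − 0.20) = 8.0, power 0.803.
- Not an F-test: an absolute difference of 0.20 in quit rates with a control rate near 19% (19% vs 39%) has power 0.802 at 80 per arm.
- Not an F-test: a one-sided alpha of 0.05 comes close, at N = 156.

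**The scale of the outcome.** The documents give no quit rates, so control rates are assumed here. The pooled two-proportion test has power Φ{[|p₂ − p₁|√n − 1.96√(2p̄(1 − p̄))] / √(p₁(1 − p₁) + p₂(1 − p₂))}. For 15% vs 33.9% with n = 80:

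- |p₂ − p₁|√n = 0.189 × 8.944 = 1.690.
- p̄ = 0.2445, so 1.96 × √0.3694 = 1.191.
- The denominator is √(0.1275 + 0.2241) = 0.593.
- (1.690 − 1.191) / 0.593 = 0.84, which is 80% power.

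Solved in the same way for other control rates:

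| Control quit rate (assumed) | Intervention rate for 80% power, 80 per arm | Odds ratio |
|---|---|---|
| 10% | 27.1% | 3.3 |
| 15% | 33.9% | 2.9 |
| 20% | 40.2% | 2.7 |

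The odds ratio in the first row is (0.271/0.729) / (0.10/0.90) = 3.3, and likewise for the others. A small effect on this scale (h = 0.20, for example 15% vs 22.8%) has about 24% power.

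**The case against.** The strongest defence is that the sponsor may have used a G*Power setting that the article does not report. Two settings fit parts of the plan. Covariate adjustment is planned, and an R-squared of 0.20 gives exactly 160. The primary GEE covers post-intervention and follow-up, that is t1, t2 and t3, and three waves with r = 0.7 also give 160.

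This stands in part. A reader might infer that the sponsor miscalculated, and the article does not prove that. Nor can the three-wave route be dismissed on the ground that every woman smokes at t0: that argument removes only routes that use t0. What remains against the repeated-measures route is that it tests an average over waves, while the sample size section ties its claim to t1. The R-squared route rests on a figure that appears nowhere.

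A reader might also infer that the trial can detect only a large effect. That is too strong. Under the f or w reading the shortfall is modest: f of about 0.223 is detectable against the stated 0.20. The 24% figure depends on the d reading, which is supported by the description of 0.20 as small but not by the choice of an F-test. On the quit-rate scale, 80 per arm gives at least 80% power for a 20-point difference if the control rate is about 19% or lower. The mismatch of test and endpoint therefore does not by itself show that power is inadequate.

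Finally, a reader might count the absence of a dropout allowance as an error. A condensed article may leave that to the full protocol, so it is not one.

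**Conclusion.** The point holds in this form: 160 cannot be reproduced from the inputs the article states, and the F-test effect size does not match the binary endpoint or the logistic GEE. For a two-group F-test at t1, 200 women are needed under Cohen's f, 25% more than 160 (200/160 = 1.25). Power at 160 is about 71% under f and about 24% under d. The claim of 80% power for a small difference at t1 is not delivered by the design as stated.

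The power figures rest on the stated alpha, power, test and single time point, with all 160 women evaluable. The quit-rate figures rest also on assumed control rates and on an unadjusted two-proportion test.

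**What to change.** Keep 160 and revise the Sample size calculation section:

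1. Name the effect-size metric and the G*Power procedure and settings actually used, including any number of waves, correlation or R-squared.
2. Restate the detectable effect as two quit rates over a range of control rates marked as assumed. For example: with 80 evaluable women per arm and two-sided alpha 0.05, there is 80% power at t1 for about 10% vs 27%, 15% vs 34% or 20% vs 40%. Because enrolment has begun, label this as a restatement for the fixed sample size, not as the a priori calculation. Say also that it is an unadjusted approximation to the planned covariate-adjusted GEE.
3. Delete the claim of 80% power for a small difference with effect size 0.20 at t1.
4. Note in the trial report that a non-significant result does not exclude smaller differences.

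Loss to follow-up can be added as an assumed sensitivity range. At 20% loss (64 evaluable per arm) the pairs become about 10% vs 30%, 15% vs 36% and 20% vs 43%.

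The cost is wording only, with no extra participants and no change to the analysis. The downside is that the stated figure becomes less favourable.
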